**10.4.1.2 Secondary Efficacy Parameters**

Efficacy will be estimated by comparing the time to symptom clearance, and haemoglobin concentration at day 14 between the Cotrifazid and comparator groups. Survival curves showing the clearance time will be plotted for the two groups, and compared using the logrank test. The t test will be used to compare means of haemoglobin concentration between the two groups.

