5. Comparison of the haematological concentration in the Cotrifazid and comparator groups

TOLERANCE:

1. Comparison of the rate of adverse events in the Cotrifazid and comparator groups
2. Comparison of the type of adverse events in the Cotrifazid and comparator groups
3. Comparison of the rate of patients requiring an additional drug because of tolerance problems in the Cotrifazid and comparator groups (e.g. antivomiting)
4. Comparison of the biochemical and haematological results in the Cotrifazid and comparator groups

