**3.3 Exclusion Criteria**

A subject is not eligible if one or more of the following parameters are fulfilled:

- History of allergy to drug compounds
- Unable to swallow
- Signs of severe malaria (i.e. history of recent convulsion, any neurological sign or impairment of consciousness, temperature >40 C0, heavy vomiting, , haemoglobinuria, respiratory distress, bleeding, circulatory collapse, shock, jaundice, haemoglobin < 5 g/dl)
- Contra-indications for Lariam (history of psychiatric disorder, epilepsy)
- Less than 6 months of age
- Pregnancy

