**5.2 Assessment of Safety**

**5.2.1 Safety Parameters (including Laboratory Evaluations)**

The prime measurement of safety in this trial is the close observation of the subjects. All subjects will be followed clinically every day for the first 4 days, and longer in case of complication. All subjects will be seen at day 7 and 14 to identify late adverse events or clinical failure.

Laboratory measurements : AST and ALT will be measured at Day 0 and 7, haemoglobin concentration at day 14.

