## In this study AEs will be measured against the medical history, baseline physical examination and laboratory baseline values.

## AEs should be described by severity, intensity and relationship to the compounds under study as well as the method by which the information was obtained (observed, elicited or spontaneously reported).

The severity/intensity of adverse events is graded on a 3-point scale as follows:

**MILD:** Discomfort noted, but no disruption to normal daily activities.

**MODERATE:** Discomfort sufficient to reduce or affect normal daily activities.

**SEVERE:** Inability to perform normal daily activities.

**All** adverse events encountered during the clinical trial will be reported in the case report form.

An **adverse event** is defined as any adverse change from the subject's baseline pre-treatment condition (signs and symptoms at baseline), which occurs after chemotherapy has started, whether considered related or not to the drug. This includes clinically relevant laboratory abnormalities and intercurrent illnesses which occur or worsen during the study period.

The intensity of adverse events will be graded on a three-point scale (mild, moderate and severe) and described in detail, along with the investigator's assessment of the relationship of the event to treatment.

The investigator's assessment of the event's relationship to the trial treatment should be defined according to the following standard statement:

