**10.4.2 Primary Safety Parameters**

Rates of acute and subacute AEs by severity and relation to the drug will be compared between the Cotrifazid and the comparator groups. Laboratory parameters (haematological) in the two groups will be compared.

The Mantel-Haenzel Chi-square test (x2=0.05, two-tailed) will be used to assess any significant difference between the two groups in terms of number of AEs reported.

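### Day-14 haemoglobin is compared without the day-0 value that eligibility and adverse-event rules presuppose, and section 10.4.2 omits the biochemistry comparison that the synopsis plans

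*Protocol*

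**What the plan says.** **Haemoglobin schedule.** Section 5.2.1 of the protocol reads: "Laboratory measurements : AST and ALT will be measured at Day 0 and 7, haemoglobin concentration at day 14". Section 2.1 places the haematological assessment at day 14 only, and the secondary efficacy paragraph of section 5.3 takes haemoglobin from day-14 samples.

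**Haemoglobin analysis.** Section 10.4.1.2 names the endpoint, "Efficacy will be estimated by comparing the time to symptom clearance, and haemoglobin concentration at day 14 between the Cotrifazid and comparator groups", and then the method: "The t test will be used to compare means of haemoglobin concentration between the two groups". It names no covariate.

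**Where a day-0 value is presupposed.** Sections 2.1 and 3.3 exclude patients on a numeric threshold: "shock, jaundice, haemoglobin < 5 g/dl". Section 5.2.2 says that "AEs will be measured against the medical history, baseline physical examination and laboratory baseline values", and it counts relevant laboratory abnormalities that arise or get worse during the study as adverse events.

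**Biochemistry.** AST and ALT have a scheduled before/after pair, at days 0 and 7. In the synopsis, the fourth tolerance item is "Comparison of the biochemical and haematological results in the Cotrifazid and comparator groups". Section 10.4.2, which sets out the safety analysis, says only: "Laboratory parameters (haematological) in the two groups will be compared".

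**The concern.** There are two separate issues.

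The first is that the protocol needs a haemoglobin value at entry for two purposes but schedules and analyses none. Patients range from infants of 6 months to adults and all had a treated malaria episode in the last 28 days, so entry haemoglobin can be expected to vary and to be related to the day-14 value. An unadjusted comparison leaves that variation in the error term. Haemoglobin is also the only haematological measure scheduled, and haematology is the only laboratory comparison that section 10.4.2 names. If the day-0 value is not kept, a low day-14 result cannot be classed as a worsening under the definition in section 5.2.2. A later analysis plan could add a covariate, but it could not recover a value that was never recorded.

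The second is that the synopsis and section 10.4.2 disagree about biochemistry. An analyst who follows 10.4.2 as written would not compare the liver enzymes between arms, although they are the only laboratory measures with a scheduled before/after pair. Section 1.2 makes safety a primary parameter alongside efficacy.

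**Working it through.** **1. Setting the passages side by side**

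| Item | Needed or collected | Scheduled | Analysed |
|---|---|---|---|
| Haemoglobin, day 0 | Needed for exclusion below 5 g/dl (2.1, 3.3) and as laboratory baseline (5.2.2) | Not listed | Not used |
| Haemoglobin, day 14 | Secondary efficacy (5.3) and laboratory safety | Yes (2.1, 5.2.1, 5.3) | t test of means (10.4.1.2); haematology (10.4.2) |
| AST/ALT, days 0 and 7 | Safety | Yes (5.2.1) | In the synopsis; not in 10.4.2 |

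**2. Inputs for the precision calculation**

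- The protocol states no precision or power figure for haemoglobin, so there is none to reproduce. The 110 per arm in the sample size section was set on cure rate, and nothing here depends on how it was derived.
- Evaluable patients per arm: 110 less the stated 10% loss, 110 × 0.90 = 99.
- Two-sided 0.05 and 80% power are my choice, because the protocol sets neither for haemoglobin: 1.960 + 0.842 = 2.802.
- The haemoglobin SD is not given, so results are in SD units.
- The day-0/day-14 correlation ρ is not given. I assume 0.3, 0.5 and 0.7.

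**3. Unadjusted t test**

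Detectable difference = 2.802 × √(2/99) = 2.802 × 0.1421 = 0.398 SD.

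**4. Analysis of covariance on day-0 haemoglobin**

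The residual variance is multiplied by 1 − ρ², so the detectable difference is 0.398 × √(1 − ρ²). The number per arm that matches the unadjusted precision of 99 is 99 × (1 − ρ²), rounded up.

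| Assumed ρ | Variance removed (ρ²) | Detectable difference | Power at 0.398 SD | Matching n per arm |
|---|---|---|---|---|
| none (t test) | 0% | 0.398 SD | 80% | 99 |
| 0.3 | 9% | 0.380 SD | 83.6% | 91 |
| 0.5 | 25% | 0.345 SD | 89.9% | 75 |
| 0.7 | 49% | 0.284 SD | 97.5% | 51 |

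These are large-sample figures with a common SD and correlation across arms.

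**5. Biochemistry**

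No arithmetic applies. The two statements differ in scope: the synopsis covers biochemical and haematological results, section 10.4.2 only the latter. Both cannot govern the analysis.

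**The case against.** The strongest reply on haemoglobin is that the protocol has chosen a valid test. The arms are randomised, so a day-14 comparison is unbiased on average, and its standard error already allows for chance differences at baseline. A reader might infer that the missing baseline biases the result; the documents do not support that. The cost is efficiency, on a secondary parameter for which the trial was not sized. All of this stands.

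It can also be said that the day-0 value may well be recorded. The case report form is not shown, section 2.1 lists only follow-up assessments, and the exclusion implies that someone measures haemoglobin at entry. This stands in part: the documents do not show that the value will be lost. But 5.2.1 gives day 0 for AST/ALT and only day 14 for haemoglobin in the same sentence, so the text does not secure it.

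A third reply is that covariates and transformations are usually left to an analysis plan. That would hold if the protocol were silent. Here it names the test and restricts the laboratory comparison, and an analysis plan cannot supply a baseline that was not kept.

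On liver enzymes, a reader might infer that they are left out of the safety analysis altogether. That goes too far. The synopsis plans the comparison, and clinically relevant enzyme rises also count as adverse events, whose rates 10.4.2 compares between arms. What remains is a conflict of scope between two parts of the protocol.

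**Conclusion.** The point holds as a should-fix matter of consistency and precision, not as a validity problem.

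- **Haemoglobin.** The protocol presupposes a day-0 value in two places, schedules none, and fixes an analysis that does not use one. The precision forgone is 9% to 49% of the variance for an assumed correlation of 0.3 to 0.7. At the low end the gain is small (0.398 to 0.380 SD); at the high end it is large (0.398 to 0.284 SD). Nothing in the protocol tells us where in that range the trial lies, and the figures assume about 99 evaluable patients per arm. It would be wrong to say that baseline explains most of the day-14 spread: even at 0.7 the share is 49%. The firmer loss, which does not depend on the correlation, is that a change in haemoglobin cannot be assessed unless the day-0 value is recorded.
- **Biochemistry.** The synopsis and section 10.4.2 conflict and must be reconciled. This conclusion rests on the text alone.

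**What to change.** 1. **Section 5.2.1:** list haemoglobin at day 0 as well as day 14, and record on the case report form the value that eligibility already requires.
2. **Section 10.4.1.2:** replace the t test by analysis of covariance of day-14 haemoglobin on arm and day-0 haemoglobin, for Cotrifazid against each comparator.
3. **Section 10.4.2:** add biochemistry so that it agrees with the synopsis, comparing day-7 AST and ALT on the log scale between arms, adjusted for the day-0 value.

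The cost is one case report form field, a few sentences of protocol text and slightly more analysis work. Section 5.2.1 already provides for AST/ALT at day 0, and the exclusion criterion already calls for a haemoglobin value. The first step must be in place before enrolment, since a missed baseline cannot be recovered; the other two can be settled at any time before the data are analysed.

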**10.4.2 Primary Safety Parameters**

Rates of acute and subacute AEs by severity and relation to the drug will be compared between the Cotrifazid and the comparator groups. Laboratory parameters (haematological) in the two groups will be compared.

The Mantel-Haenzel Chi-square test (x2=0.05, two-tailed) will be used to assess any significant difference between the two groups in terms of number of AEs reported.

**10.5 Data Management and Analysis**

Data cleaning and entry will be done in Madang, under the supervision of [name] and [name].

Weekly and monthly backups on tapes, the latter being kept in Maprik and Madang will be made.

Data analysis will be done by [name], and [name] (PNGIMR, STI).

Discussion of analysis will involve all collaborating persons.

All papers will include representatives of PNGIMR and STI.

